### Trial interventions

#### AVATAR_VRSocial

AVATAR_VRSocial is an augmented version of the AVATAR therapy (as delivered in Craig *et al*^17^) by adding three additional sessions supported by immersive VR technology. Therefore, this therapy consists of a total of 10 sessions (see table 2).

**Table 2 T2:** Summary of the sessions including in AVATAR_VRSocial therapy

	Short description	Number of sessions
AVATAR therapy	Three-way dialogue between participant, avatar and therapist	Seven sessions (six sessions of + one assessment and avatar creation session)
Virtual Reality social scenarios	Interaction with social agents during quotidian situations+personalised negative voice	Three sessions

AVATAR therapy works by facilitating a novel therapeutic context in which a ‘face-to-face’ dialogue between the person and a computerised representation of their voice is facilitated by a therapist. Bespoke software transforms the therapist’s voice to match the pitch and tone of the chosen voice, and the person creates a visual representation of their voice. The voice and image are combined to produce the ‘avatar’ (ie, an animated talking virtual agent with enhanced lip-sync speech and eye blinking), through which the therapist interacts with the voice-hearer, in a three-way dialogue (for further details on the software, please see https://www.avatartherapy.co.uk/). Using this platform, the therapist can speak to the client in their normal voice or in the chosen avatar voice which is a modified version of their normal voice. Where there are multiple voices, the participant selects one to work with (usually the most dominant, frequent and distressing). The embodiment of the voice is enhanced using direct verbatim speech, and enactment of the ascribed character and background of the voice. A comprehensive account of therapeutic targets of AVATAR therapy showed that some therapeutic targets were clearly present for all therapy completers (power and control, self-esteem and future focus), whereas others (eg, maintenance processes, working with trauma, experiential disengagement) were identified in some but not all participants, in line with the tailoring of the intervention to an individualised formulation.^44^

AVATAR therapy as delivered within the pilot work and AVATAR1 trial consists of a total of six sessions (in addition to an initial clinical assessment session including avatar creation) and comprises two phases. In the first phase (Exposure and Assertiveness), the avatar delivers verbatim voice content (including threats and abuse) and the person practices assertive responding. Over time the avatar becomes less hostile as the person develops increased power and control within the dialogue. This cues a second phase with formulation-driven therapeutic targets, which can include work on beliefs about voices, self-concept and trauma. Each AVATAR therapy session consists of three parts: pre-dialogue, active dialogue and post-dialogue debrief. The pre-dialogue and post-dialogue are important for cueing and consolidating key change processes occurring in the dialogue with the avatar. The active dialogue duration is approximately 5 min in early sessions, increasing to 10–15 min in later ones. Participant and therapist are in separated rooms but in constant communication for this part of the session.

For AVATAR_VRSocial, three social virtual scenarios have been created to facilitate generalisation of AVATAR therapy learnings into management of the voice hearing experience during social interactions. The scenarios include (1) taking a bus ride in a full bus, (2) looking for specific groceries in a full supermarket and (3) talking to the receptionist at a doctor’s practice. Each scenario has a specific task to be accomplished by the person. Some responses from the virtual agents are automated and modulated by the person’s verbal response. During the social interaction, the person experiences their personalised voice (ie, the transformed voice matching the voice that distresses them). The aim is to practise taking control of the voices by training what they learnt during the dialogues (eg, disengaging from voices, postponing the conversation) as well as refocusing on the social interactions. The therapist can see and hear everything that is occurring in the VR environment as well as the participant’s responses. Mirroring the avatar dialogues, they will be able to communicate with the participant directly within the VR environment using their own voice, offering support during the interactions. The VR sessions are delivered over three individual sessions assisted by these VR environments.

The virtual scenarios are presented using a wireless head-mounted display (Pico 4) with a resolution of 2160 × 2160 pixels per eye, 122.16° diagonal field of view and mounted headphones. The personalised negative voice is exported from the AVATAR therapy platform to the VR scenarios. The therapist can trigger the negative voice at random intervals (determined by the system) or at his/her own demand depending on the person’s performance. As per the AVATAR therapy sessions, the three VR sessions consisted of three parts: the pre-VR discussion with the therapist, the immersive part using the VR headset (lasting approximately 10 min) and the post-VR debrief with the therapist. The person can request to stop the immersive experience at any point.

At the end of the final session, participants will be asked to complete a self-reported questionnaire to assess the acceptability of the intervention.^43^ The number of active sessions attended (ie, sessions involving active avatar dialogue or VR practice) by the participant will be measured to assess treatment adherence. Fidelity to the clinical manual will be assessed by the therapist by completing a session-by-session checklist of specified targets (these will also be used during training and ongoing supervision; see above). Each session will be audio-recorded with consent. Therapist competence, after completion of training, will be assessed by an expert in AVATAR therapy for general/clinical and avatar-specific skills using ratings adapted from the first AVATAR therapy trial and allowing for differing skill requirements for each level of therapy.

#### Treatment as usual

Participants who are allocated to the TAU arm will continue to receive their usual care. TAU for the participants in this trial will typically consist of medication management, supportive brief counselling sessions and various types of psychosocial support (eg, social work guided support, peer support) and monitoring provided by mental health services, with individual and family psychological therapies offered occasionally. TAU will vary across individuals and clinical teams. Efforts will be put into collecting detailed data on TAU.

Participation will not alter usual treatment decisions about medication and additional psychological and psychosocial interventions, which remain the responsibility of the clinical team. The antipsychotic medication prescribed to participants in the study and psychological and psychosocial interventions provided will be recorded.

### Adverse events

The occurrence of AEs will be monitored actively and systematically, following guidance from the Consolidated Standards of Reporting Trials (CONSORT)^45^ with the extension for social and psychological interventions, and the extension for reporting of harms. AEs are defined as any untoward medical occurrence, unintended disease or injury, or untoward clinical signs in service user/patient participants, whether or not related to the therapy or device which require additional support or input from health professionals. AEs will be initially assessed at three levels of intensity: mild, moderate and severe, which reflect the impact of the event on the person at the time. Please note there is a distinction between ‘severe’ and ‘serious’. Seriousness is the criteria for defining regulatory reporting obligations and the following will be considered as serious adverse events (SAE, categories A–C): all deaths (category A), incidents which acutely jeopardise the health or psychological well-being of the individual, resulting in immediate hospital admission and/or permanent disability (category B) or resulting in injury requiring immediate medical attention (category C).

In any case of an SAE, the CI must be notified within one working day by a member of the trial team becoming aware of the event. The CI (or a clinically qualified delegate) will review all SAE reports received. The CI will keep investigators informed of any safety issues that arise during the course of the trial. The CI is responsible for reporting fatal and life-threatening serious adverse reactions to the competent authorities within 7 days of the CI becoming aware of the event. The TSC will be informed of serious adverse reactions periodically. The chair of the TSC will determine the relatedness of the event to the research assessment, therapy or device based on a temporal relationship, and consideration of whether there were insufficient or inadequate instructions for use, deployment, installation or operation, or any malfunction of the AVATAR software. An AE may also be device-related if it was the result of user error or intentional misuse of AVATAR therapy software. As detailed in the risk analysis conducted for the CE-marking of AVATAR therapy software, we do not anticipate any serious adverse device effects. We do not anticipate any serious therapy or assessment-related AEs; this expectation is based on the safety data from the previous AVATAR trials.^17 19^ Reasons for withdrawal from the study will be recorded. For the final reports of the trial, the numbers, types and severity of AEs by trial condition, as well as discontinuations, will be reported using descriptive statistics.

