## Objectives

The primary objective is to assess the feasibility and acceptability of a targeted intervention to improve voices related distress, and social avoidance and distress in people at early stages of psychosis (FEP<5 years^24^). The second main research objective is to convene evidence on clinical outcomes to provide first estimates of efficacy of this enhanced version of AVATAR therapy (AVATAR_VRSocial) in a sample of German individuals with early psychosis, which can inform subsequent development and testing of the therapy. Table 1 summarises the objectives of the study and includes the associated feasibility markers and assessment measures.

**Table 1 T1:** Summary of objectives and related assessment measures

	Objectives	Measures
Primary	Assessing feasibility and acceptability of AVATAR_VR psychotherapy for people who experience distressing voice hearing	Number of patients referred to the study, consented, declined and retainedCompletion rates of each assessment measure and retention at follow-up assessmentsNumber and proportion of consenting participants within AVATAR_VRSocial condition who reach the point of therapy ‘exposure’ (attended at least five of nine therapy sessions)Number of adverse serious and non-serious adverse events in each condition
Secondary	Clinical information about preliminary estimates of clinical effectiveness of AVATAR_VRSocial in addition to treatment as usual vs treatment as usual alone in people in early stages of psychosis	Voice distress, frequency and severity of voices: PSYRATS-AHSocial anxiety and avoidance: O-AS, O-CDQOther voices measures: BAVQ-R; VPDS; Brief assessment of negative hallucinations when outsidePsychiatric symptoms: PSYRATS-DEL, DASS-21. CAINS, Rosenberg-Self-EsteemQuality of life: EQ-5D-5L
Qualitative	Assessing acceptability	AFIMFeedback from Qualitative Interview

AFIM, Acceptability and Feasibility of Intervention Measure; BAVQ-R, Beliefs About Voices Revised; CAINS, Clinical Assessment Interview for Negative Symptoms; DASS21, Depression Anxiety and Stress Scales; EQ-5D-5L, EuroQol BIOMED Research Programme; O-AS, Oxford—Agoraphobic Avoidance Scale; O-CDQ, Oxford Cognitions and Defences Questionnaire; PSYRATS-AH, Psychotic Symptoms Rating Scale—Auditory Hallucinations; PSYRATS-DEL, distress and frequency factors, and total scores on the delusional beliefs subscale of the Psychotic Symptoms Rating Scales; VPDS, Voice Power Differential Scale.

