#### Exclusion criteria

Primary diagnosis of substance disorder, personality disorder or learning disability.AVHs secondary to an organic disorder.Currently participating or being confirmed to participate in another interventional study in which they are receiving an intervention which uses psychological therapy and focuses on voices.Profound visual/hearing impairment or insufficient comprehension of German to be able to engage in assessment or therapy.Currently experiencing an acute mental health crisis (ie, being at immediate and serious risk to self or others).

Participants have the right to withdraw from the study at any time for any reason. All efforts will be made to report reasons for withdrawal. If they wish to withdraw from the therapy only, all efforts will be made to obtain follow-up data. The chief investigator (CI) also has the right to withdraw patients from the study in the event of clinical contraindications: the intervention may be discontinued if the participant requests this or if the clinician judges, in consultation with the wider supervisory team, that the intervention is associated with a significant worsening of mental health. In this case, an adverse event (AE) form would also be completed. It is understood by all involved that an excessive rate of withdrawals can render the study uninterpretable; therefore, unnecessary withdrawal of participants should be avoided. Should a participant decide to withdraw from the study, all efforts will be made to report the reason for withdrawal as thoroughly as possible. Should a participant withdraw from therapy only but not from the study, efforts will be made to continue to obtain follow-up data and assess reasons for dropping out, with the permission of the patient.

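### A hospital admission is serious only if it is *immediate*, so an unplanned psychiatric admission arranged after a delay is classed as a non-serious adverse event

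*Protocol article*

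**What the plan says.** The Adverse events section separates severity (mild, moderate or severe) from seriousness and gives seriousness its own purpose: "Seriousness is the criteria for defining regulatory reporting obligations". It then lists what counts as serious:

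- Category A: "all deaths (category A".
- Categories B and C share a lead-in, "incidents which acutely jeopardise the health or psychological well-being of the individual", and differ in the outcome required.
- Category B: "resulting in immediate hospital admission and/or permanent disability (category B".
- Category C: "resulting in injury requiring immediate medical attention (category C".

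The list stops there. Admission occurs only in category B and only with the word *immediate*, which the article does not define.

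Two things depend on the classification. The same section states: "In any case of an SAE, the CI must be notified within one working day". It also has the chief investigator, or a clinically qualified delegate, review all SAE reports. Table 1 (Objectives) includes among the measures of the primary objective: "Number of adverse serious and non-serious adverse events in each condition".

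**The concern.** A harm that the article itself anticipates is psychiatric worsening. The withdrawal paragraph under Exclusion criteria allows the intervention to be discontinued if the clinician judges that "the intervention is associated with a significant worsening of mental health". The description of AVATAR_VRSocial has the avatar voice threats and abuse taken from the participant's own voice-hearing. Worsening of this kind need not end in admission on the same day. It can build up, and an admission can be arranged over several days.

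If the label *serious* depends on how quickly the admission follows, the serious-event count reflects admission logistics as well as harm. Two consequences are at stake: whether the chief investigator hears of the event promptly and reviews it as an SAE, and whether it enters the serious half of a count reported by condition.

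**Working it through.** The article states no admission or SAE rate, so there is no figure to reproduce. The check applies the definitions to two cases.

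**Inputs.** The three SAE categories and the notice and review rules come from Adverse events, the count by condition from Objectives (Table 1), and the 20 per arm from Analysis.

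**Test.** Take two participants with the same psychotic worsening. Both need an unplanned admission, and neither dies, is permanently disabled or is injured in a way that needs immediate attention. Only the interval to admission differs.

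| Question | Admitted at once | Admitted after a delay |
|---|---|---|
| Category A (death)? | No | No |
| Category B (acute jeopardy and immediate admission, or permanent disability)? | Yes | No: the admission is not immediate |
| Category C (injury)? | No | No |
| Classification | SAE | Non-serious adverse event |
| Notice within one working day | Yes | Not required |
| Chief investigator review of an SAE report | Yes | Not required |
| Table 1 count | Serious | Non-serious |
| Reported by type and severity, by condition | Yes | Yes |

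The two cases differ in timing alone, yet they fall on opposite sides of the serious/non-serious split. The acuteness condition in the lead-in works in the same direction: worsening that develops gradually may fail it even before the speed of admission is considered.

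Grading the delayed case as *severe* does not repair this, because the article says that severe and serious are different things.

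**Size.** One participant in an arm of 20 is 1/20 = 5% of the arm. If each event falls in a different participant, re-labelling one changes the proportion with a serious event by 5 percentage points.

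Any estimate beyond that needs assumptions that the documents do not supply. As an illustration only, assume 2 to 4 psychiatric admissions in an arm, 25% to 50% of them not immediate:

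- Low end: 2 × 0.25 = 0.5 events left out of the serious count.
- High end: 4 × 0.50 = 2 events left out.

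The share left out, 25% to 50%, is simply the assumed fraction. The illustration shows how few events are involved. It does not estimate the undercount.

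**The case against.** **The source is a condensed article.** The trial runs under a full protocol (V.1.2, cited in Trial status), which may define *immediate* or give classification guidance. An assessor might also read the word as meaning unplanned. This is a fair caution. But the article states an explicit definition rather than leaving it to another document, and nothing in its text supports reading *immediate* as unplanned. If assessors are free to choose, a primary-objective measure rests on individual judgement.

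**Harm data are not lost.** This stands. A reader might infer that deferred admissions disappear from the trial's safety record, and the documents do not support that. Adverse events are monitored actively and include anything that calls for extra help from a health professional. They are reported by type and severity for all randomised participants, by condition. What is lost is the serious label and what follows from it.

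**There is another route for the named harm.** Also true in part. If the therapy is judged to be causing significant worsening, the clinician consults the supervisory team, the intervention may be discontinued and an adverse event form is completed. That route covers the therapy arm only and does not trigger the SAE notice.

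**No decision rule uses the SAE count.** Correct. The progression criteria named in Analysis concern recruitment, retention and treatment uptake, and there are no interim analyses or formal stopping rules. The classification therefore changes no stated go/stop decision. Table 1 still lists the count under the primary objective.

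**Prolonged stays are marginal.** Agreed. Recruitment is mainly through referral by medical professionals, including outpatient departments and private practitioners, and people in acute crisis are excluded at entry. Prolongation belongs in the revised wording for completeness.

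**Conclusion.** The point holds on the wording. An unplanned psychiatric admission arranged after a delay, with no death, permanent disability or injury needing immediate attention, is a non-serious adverse event. It therefore falls outside the one-working-day notice, the chief investigator's review of SAE reports and the serious count in Table 1.

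Three stronger readings are tempting and should not be drawn:

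- *That worsening is never serious, however severe.* Death, permanent disability and injury needing immediate attention qualify on their own terms.
- *That the serious count is halved, or short by some other known amount.* The documents give no rate of admission or delay, so the undercount cannot be derived. They support only the statement that one event weighs visibly in an arm of 20.
- *That the between-arm comparison is biased.* The same wording applies to both arms, and nothing shows that delays differ between them.

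The conclusion assumes that the article's SAE list is the one in use and that *immediate* is applied in its ordinary sense. On that footing this is a definitional weakness in a safety measure. It is worth correcting, and it does not threaten the trial's feasibility conclusions.

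**What to change.** In category B, replace the phrase about immediate admission with: any unplanned hospital admission (or prolongation of one), whatever the interval from onset. For admissions, drop the requirement that the jeopardy be acute. Keep planned admissions for pre-existing reasons excluded. This changes how events are classified and reported, not how participants are treated.

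Apply the new wording to adverse events already recorded, in both arms, so that the Table 1 count rests on one definition throughout. This needs to be known for each recorded admission: whether it was planned, and if so for what reason. If the full protocol already defines the term in this sense, it is enough to cite that definition and align the text.

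The cost is an amendment, which under Ethics and dissemination goes to the same ethics committee, plus re-classification of the recorded events and slightly more SAE reports to process. Recruitment was planned to end in April 2025, so part of the work is retrospective. Data collection is planned to run to September 2026, so the wording would also govern events still to come.

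### The 7-day rule names life-threatening serious adverse reactions, but the closed SAE list has no life-threatening category, so a near miss without a listed outcome is not an SAE

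*Protocol article*

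**What the plan says.** All the rules are in the protocol article, under Adverse events.

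- **What seriousness decides.** "Seriousness is the criteria for defining regulatory reporting obligations". The section separates this from severity, which is graded mild, moderate or severe.
- **What is serious.** Category A is all deaths. Categories B and C share one stem, "incidents which acutely jeopardise the health or psychological well-being of the individual", followed by the outcomes that complete them: "resulting in immediate hospital admission and/or permanent disability (category B) or resulting in injury requiring immediate medical attention (category C").
- **What an SAE sets in motion.** "In any case of an SAE, the CI must be notified within one working day"; the chief investigator or a clinically qualified delegate then reviews the report.
- **What goes to the authorities.** The chief investigator reports "fatal and life-threatening serious adverse reactions" within 7 days of becoming aware of the event.

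Table 1 lists the number of serious and non-serious adverse events in each condition among the measures for the primary objective.

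**The concern.** The expedited rule names two kinds of reaction, and only one of them has a counterpart in the definition that controls entry to the reporting pathway. An event that put life at risk but ended without a listed outcome falls between the two rules.

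Two things are at stake. The first is timely safety oversight. The therapy has the avatar deliver verbatim voice content, including threats and abuse, to people with distressing voices, and the Analysis section plans no interim analyses or formal stopping rules. The SAE notice is therefore the main prompt safety channel that the article describes. The second is the split between serious and non-serious events by arm, which the trial will report under its primary objective and which depends on this definition.

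**Working it through.** No arithmetic applies. The check sets the definition against the rules that depend on it.

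**Step 1: map the 7-day rule onto the list.** Fatal corresponds to category A. For life-threatening, the nearest wording is the stem shared by B and C, which speaks of acute jeopardy. That stem has no letter of its own. It counts only when joined to an outcome: admission or permanent disability for B, injury needing immediate attention for C. Jeopardy alone is not enough.

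**Step 2: look for another way in.** The term life-threatening occurs once in the article, in the 7-day sentence, and is not defined. It is not an intensity grade. Grading the event severe does not help, because the section expressly distinguishes severe from serious.

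**Step 3: run the possible cases through the rules.**

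| Life-threatening or fatal event that ends in | Category | SAE? | One-working-day notice | 7-day report if judged a reaction |
|---|---|---|---|---|
| Death | A | Yes | Yes | Yes |
| Immediate admission or permanent disability | B | Yes | Yes | Yes |
| Injury needing immediate medical attention | C | Yes | Yes | Yes |
| None of these | None | No | No | No |

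The last row is the gap. It includes events with an injury that does not need immediate attention, as well as events with no injury. An interrupted suicide attempt without injury or admission would be an example, provided the trial regards it as life-threatening; since the term is undefined, that is an assumption.

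**Step 4: follow the last row through.** An event that is not an SAE cannot be a serious adverse reaction, so the 7-day duty does not arise. The 7-day clock also starts when the chief investigator becomes aware, and the only deadline for making the chief investigator aware of an event is the SAE notice.

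**Step 5: see where the event is counted.** The AE definition is limited to occurrences that require additional support or input from health professionals. If the near miss meets that condition it is a non-serious AE; if not, it is not an AE under the definition at all.

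**The case against.** The strongest reply is that the two sentences can both be obeyed. The 7-day sentence concerns serious adverse reactions, so it can be read as selecting a subset: classify by A to C first, then expedite those that were fatal or life-threatening. This stands. A reader might infer that the sentences flatly contradict each other, or that every life-threatening event carries a 7-day report. The text supports neither: the rule covers only events that are both serious and related. But the subset reading leaves the subset undefined and leaves the last row of the table outside the pathway.

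The second reply is that B and C will catch most life-threatening events. That also stands, and it limits the size of the point. It does not remove it, because both categories require an outcome that a near miss lacks. The article's Exclusion criteria treat immediate and serious risk to self or others as a state in its own right; the SAE list has no equivalent.

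Third, a reader might infer that such an event would vanish from the safety data or could never come to the chief investigator's attention. That goes too far. AEs are monitored actively and reported by arm with type and severity, so a recorded near miss would move between two reported rows and would not be lost. Under the withdrawal provisions, worsening attributed to the intervention is discussed with the supervisory team. Data handling provides for informing health professionals of disclosed risk. What is lost is the mandatory, timed trigger.

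Finally, the article condenses a full protocol (V.1.2) that is not shown and may define the term. This is a partial defence only: the article prints both the complete lettered list and the 7-day rule, and as printed they do not match.

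**Conclusion.** The point holds as a mismatch between two stated rules. The closed SAE list has no place for the life-threatening class that the 7-day sentence names, and a life-threatening event without a listed outcome triggers neither the notice nor the report. It would be counted as a non-serious AE at most.

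The gap is narrow, and no figure can be put on it, because the article gives no expected rate of such events. A reader might try to infer a size from the 20 participants per arm, but the precision of an event proportion in an arm of that size is the same under either definition and does not measure this defect.

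The conclusion rests on reading the A to C list as complete, which is how the article presents it, and on the full protocol not supplying a definition that closes the gap.

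**What to change.** Reconcile the SAE definition with the 7-day sentence so that they cover the same class, and define life-threatening wherever it is kept. One way is to name life-threatening events in the SAE list. Another is to state that the 7-day rule applies only within categories A to C, in which case the near miss stays outside by explicit decision. The choice and final wording belong to the sponsor and investigators.

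Then re-check the AEs already logged against the reconciled list, in both arms alike. Recruitment began in December 2023, so some events may have been classified under the present wording; data collection is planned to run until September 2026.

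The cost is a short protocol amendment, which the Ethics and dissemination section says goes back to the same ethics committee, and a review of AE records in a trial of 40 people. If the list is widened, the SAE count may rise slightly, and the report should say that the definition was clarified during the trial.
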